### Randomization and blinding

Participants will be screened strictly according to the diagnostic criteria, inclusion and exclusion criteria for TN formulate in this trial. The uniquely eligible participants will be numbered by using IBM SPSS Statistics 25.0 software, the relevant parameters will be entered in the syntax editor, and they will be randomly divided into EA and sham EA groups in a 1:1 ratio. Due to the particularly of the acupuncture treatment, a single-blind method will be applied in this study. Importantly, the patients, outcomes assessor, and statistician will be blinded. To ensure better implementation of the blinding method, each participant will be treated individually to minimize discussion about the acupuncture treatment methods, feelings and the therapeutic effects. We will inform the patients that due to individual difference, each person may experience the stimulation differently. At the end of the 4-week treatment period, participants will be asked to indicate whether they had received real EA or sham EA. The proportions of participants who believed they received real EA will then be compared between the two groups.

### Recruitment strategies

Participants will be recruited from the Third *Affiliated Hospital of Zhejiang Chinese Medical University*, including outpatients and inpatients. Additionally, regular community recruitment will be carried out by measures such as print media and official WeChat accounts.

### Interventions

The location of acupoints are determined in accordance with the People's Republic of China National Standard, “*Interpretation of China national standard Nomenclature and Location of Meridian Points (GB/T 12346-2021)”* (32). Additionally, all acupuncturists are licensed and experienced physicians. Patients will be treated three times per week for 4 weeks, for a total of 12 EA or sham EA sessions.

#### EA group

In the EA groups, the mainly local acupoints include Baihui (GV20), Shenting (GV24), Sibai (ST2), Xiaguan (ST7), and Dicang (ST4), needles (size 0.18 mm in diameter, 25 mm in length, Hwato, Co., Ltd., Beijing, China) will be inserted. In addition, Tongziliao (GB1), Quanliao (SI18), and Jiache (ST6) will be selected to match pain in ophthalmic, maxillary, or mandibular branches, respectively. The distal acupoints will be selected by needling (size 0.25 mm in diameter, and 40 mm in length, Hwato, Co., Ltd., Beijing, China) bilateral Hegu (LI4), Waiguan (TE5), Taichong (LR3), and Sanyinjiao (SP6), as shown in Figure 3. Moreover, location of acupoints for treating TN is shown in Table 3. Notably, lesions in the ophthalmic, maxillary, or mandibular branches will be treated with EA treatment, ST7/GB1, ST7/SI18, or ST7/ST6 by using the FANGs acupuncture point nerve stimulator (FANGs-100, Hangzhou Hercules Medical Device Co., Ltd.). The distal acupoints of LI4 and TE5 were also selected. EA frequency alternating waves 2 Hz and 100 Hz will be utilized, with a treatment time of 60 min and a current intensity of 0.5 mA to 1 mA, depending on the individual's needs.

**Figure 3 F3:**
[figure not shown]
The location of acupoints used in the EA group.

**Table 3 T3:** Acupoints, stimulation, and location.

Category	Acupoints	Stimulation	Location
**Main**	GV20	MA	5 cun directly above the midpoint of the anterior hairline, at the midpoint of the line connecting the apexes of the two auricles
	GV24	MA	0.5 cun directly above the midpoint of the anterior hairline
	ST2	MA	At the infraorbital foramen
	ST4	MA	About 0.4 cun lateral to the corner of the mouth, directly below the pupil of the eye
	ST7	EA	Anterior to the ear, in the depression between the zygomatic arch and the condyloid process of the mandible
Localization of the TN attack			
The 1st trigeminal division	GB1	EA	0.5 cun lateral to the outer canthus on the lateral side of the orbit
The 2nd trigeminal division	SI18	EA	Directly below the outer canthus of the eye, in the depression on the lower border of zygoma
The 3rd trigeminal division	ST6	EA	One finger—breadth (middle finger) anterior and superior to the lower angle of the mandible, where master attaches, at the prominence of the muscle when teeth are clenched
**Distal**	TE5	EA	On the dorsal aspect of the forearm, 2 cun above the transverse crease of the wrist between the ulna and radius
	LI4	EA	On the dorsum of the hand, in the middle of the 2nd metacarpal bone on the radial side
	LR3	MA	On the dorsum of the foot, in the depression proximal to the first metatarsal space
	SP6	MA	3 cun above the medial malleolus, on the posterior border of the medial aspect of tibia

The location will be determined by the People's Republic of China National Standard, *ST7/GB1, ST7/SI18*, or *ST7/ST6* will be chosen for lesions in the 1st trigeminal division (ophthalmic branch), the 2nd trigeminal division (maxillary branch), or the 3^rd^ trigeminal division (mandibular branch) respectively, which will receive EA treatment. GV, Governor Vessel; ST, Stomach; GB, Gallbladder; SI, Small Intestine; TE, Triple Energizer; LI, Large Intestine; LR, Liver; SP, Spleen; MA, Manual Acupuncture; EA, Electroacupuncture.

#### Sham EA group

Participants in the sham EA group will receive needle insertion at non-acupoint sites located 2 cm lateral to the corresponding real acupoints, to a depth of 0.5 mm. Electrode wires that are externally intact but internally disconnected (to prevent current flow) will be used; these wires are carefully inspected and replaced for each participant. The wires are connected to the EA device and attached to non-acupoints in the vicinity of ST7/GB1, ST7/SI18, or ST7/ST6, and LI4/TE5. The device is equipped with external insulation and current leakage protection, and all equipment undergoes pre-use safety checks. To maintain blinding, the device screen and indicator lights will display the same parameters as the active treatment, but no electrical current will be delivered.

The selection of acupoints (local and distal point combination scheme), the 60-min treatment duration per session, and the selection of EA parameters with an alternating frequency of 2/100 Hz were based on our previous research (4, 33).

### Rescue medications

During all three phases of this study, including the 2-week baseline period, 4-week treatment period, and 12-week follow-up period, participants will not receive any treatment other than rescue medication. However, rescue medication will be allowed according to the Declaration of Helsinki for patients experiencing intractable pain. Participants will be allowed to take 200 mg of CBZ after meals, with a maximum dose of 600 mg per day in this study. Rescue medication was administered if the VAS score was ≥5 and persisted for more than 2 h. For each administration, the time and dose were recorded in detail. These recording procedures were predefined.

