**Figure 1 F1:**
[figure not shown]
Study design. EA, Electroacupuncture. Rescue medication will be allowed throughout the trial (baseline, treatment phase, follow-up phase), with a maximum daily dosage of 600 mg. The timing and dosage of all rescue medications will be recorded.

**Table 1 T1:** Schedule of enrolment, treatments, and assessments.

Study period	Screening	Baseline	Treatment period	Follow-up period
		Week−2-0	Week 4	Week 16
Eligibility screening	^ ***** ^			
Demographic data	^ ***** ^			
Case data	^ ***** ^			
History of TN	^ ***** ^			
History of treatment	^ ***** ^			
Inclusion criteria	^ ***** ^			
Exclusion criteria	^ ***** ^			
Informed consent	^ ***** ^			
Treatment condition			^ ***** ^	
Outcome assessment				
(1) BAI		^ ***** ^	^ ***** ^	^ ***** ^
(2) VAS		^ ***** ^	^ ***** ^	^ ***** ^
(3) BPI-facial		^ ***** ^	^ ***** ^	^ ***** ^
Safety assessment			^ ***** ^	^ ***** ^
Recurrence				^ ***** ^

^*^Required; BAI, Beck Anxiety Inventory; VAS, Visual Analog Scale; BPI-Facial, Brief Pain Inventory-Facial Scale.

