#### Exclusion criteria

Participants will be excluded for the following conditions: (1) patients with secondary TN (e.g. intracranial tumors, multiple sclerosis, etc.); (2) head injury, epilepsy, or other related neurological disorders; (3) cognitive dysfunction, aphasia, or mental disorders, and pain-impaired psychiatric disorders; (4) patients who are pregnant or breastfeeding; (5) not suitable for EA, such as being fitted with a pacemaker; (6) patients with psychogenic pain disorders. Notably, included patients received free treatment to improve compliance.

The specific inclusion/exclusion criteria of eligible TN patients are listed in Table 2.

**Table 2 T2:** Inclusion criteria and exclusion criteria of TN patients.

Inclusion criteria	Exclusion criteria
(1) Diagnosed with TN meet IHCD-3 criteria (2018)	(1) Patients with secondary TN (e.g., intracranial tumors, multiple sclerosis, etc.)
(2) Shooting pain, electric shock pain, or stabbing pain occurring in one or more branches of the trigeminal nerve	(2) Head injury, epilepsy, or other related neurological disorders
(3) Visual analog scale score ≥4 at baseline, more than three episodes per day, and occurring on at least 4 days per week	(3) Cognitive dysfunction, aphasia, or mental disorders, and pain-impaired psychiatric disorders (4) Patients who are pregnant or breastfeeding
(4) Male or female participants, age from 18 to 80 years old	(5) Not suitable for EA, such as being fitted with a pacemaker
(5) Beck Anxiety Inventory score ≥16	(6) Patients with psychogenic pain disorders
(6) Patients who are conscious, communicate normally, and willing to sign a written informed consent form	

TN, Trigeminal neuralgia; IHCD, International Classification of Headache Disorders; EA, Electroacupuncture.

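### Carbamazepine is the only permitted rescue drug, but eligibility does not screen for known hypersensitivity or contraindication to it

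*Protocol article*

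**What the plan says.** All references are to the protocol article.

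- **Other treatment.** Under Rescue medications, for baseline, treatment and follow-up: "participants will not receive any treatment other than rescue medication". Read sensibly, this means nothing beyond the assigned electroacupuncture (EA) or sham sessions.
- **Purpose of rescue.** The same section: "rescue medication will be allowed according to the Declaration of Helsinki for patients experiencing intractable pain".
- **Drug and dose.** "Participants will be allowed to take 200 mg of CBZ after meals, with a maximum dose of 600 mg per day in this study". No other drug is named.
- **Trigger.** "Rescue medication was administered if the VAS score was ≥5 and persisted for more than 2 h".
- **Figure 1 caption.** "Rescue medication will be allowed throughout the trial (baseline, treatment phase, follow-up phase), with a maximum daily dosage of 600 mg".
- **Analysis.** Statistical methods treats rescue and CBZ as the same thing, both in the time-varying covariate and in the comparison of users with non-users.
- **Eligibility.** There are six inclusion and six exclusion criteria, listed in the text and repeated in Table 2. One exclusion concerns suitability for the study device: "not suitable for EA, such as being fitted with a pacemaker". None mentions CBZ. Randomization and blinding adds: "Participants will be screened strictly according to the diagnostic criteria, inclusion and exclusion criteria for TN formulate in this trial".
- **Data at screening.** Table 1 already lists "History of treatment".

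**The concern.** Two rules are each stated in full but do not fit together. The rescue rule permits one drug and closes off others. The eligibility rule checks that a patient can safely receive EA, but not that the patient can take that drug.

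A patient known to be hypersensitive to CBZ, or with a contraindication to it, passes every written criterion. If that patient then has pain at the trigger level, the written rules offer no relief. Site staff would have to leave the pain untreated, depart from the protocol, or let the patient withdraw. The article bases rescue on the Declaration of Helsinki and, in the Discussion, says it is there to keep patients from stopping treatment. Neither aim is met for this group. In the sham arm, such a patient would also be receiving no current.

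**Working it through.** No figure in the plan is at issue, so there is nothing to reproduce. The check compares the rules with one another.

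**1. Is CBZ the only permitted rescue?** Rescue medications names one drug. Statistical methods equates rescue with that drug. The Figure 1 caption repeats the daily cap for every phase. Rescue drugs named: 1. Permitted range: 200 mg per dose up to 600 mg per day, that is 600 / 200 = 3 doses.

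**2. Does any criterion remove patients who cannot take CBZ?** The six exclusions are:
- secondary trigeminal neuralgia (TN);
- head injury, epilepsy or related neurological disorder;
- cognitive, language, mental or psychiatric disorder;
- pregnancy or breastfeeding;
- unsuitability for EA;
- psychogenic pain.

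Exclusions that mention CBZ: 0 of 6. Inclusion criteria that require CBZ to be tolerated: 0 of 6. The pregnancy exclusion may remove some patients for whom CBZ is unsuitable, but it does not address allergy or other contraindications.

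**3. How long does the gap last?** 2 weeks of baseline + 4 of treatment + 12 of follow-up = 18 weeks.

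**4. Which patients have no rescue at all?** Those who cannot take even one 200 mg dose. A patient who tolerates 200 mg but not 600 mg still has rescue at the lower dose. The gap therefore covers known hypersensitivity, contraindication, or previous inability to take 200 mg. It does not cover every patient who has had trouble with CBZ.

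**5. How many patients?** The article does not say. Its adverse-effect figures do not answer the question. The 40% to 60% in the Discussion counts any adverse effect, and so does the 43.6% at 600–800 mg/day, which meets the permitted range only at 600 mg.

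For scale only, take an assumed share p among the 60 enrolled. The expected number is 60 × p, and the chance of at least one is 1 − (1 − p)^60.

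| Assumed p | Expected number of 60 | Chance of at least one |
|---|---|---|
| 1% | 0.6 | 45% |
| 5% | 3 | 95% |
| 10% | 6 | 99.8% |
| 20% | 12 | >99.9% |

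No value of p is supported by the article. The number who also reach the rescue trigger cannot exceed the number affected.

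**The case against.** The strongest reply is that this is an omission of the kind a condensed article may leave to the full protocol or to clinical judgement. Precautions for a rescue drug could sit in a document not shown here. The sentence barring other treatment cannot be read literally, since it would bar EA itself. The CBZ wording is permissive, and nothing says that a patient unable to take it would be refused something else. The group is also narrow, because a patient must both be unable to take CBZ and have pain at the trigger level for over 2 hours.

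Part of this stands. The article does not show that anyone would be denied relief or given a drug they cannot take, and clinicians would probably act sensibly. But eligibility is not merely summarised here. The criteria are numbered, repeated in a table presented as the specific list, and said to be applied strictly. The rescue drug, dose, cap and trigger are also fixed. Under those rules, giving another drug would be a departure from protocol, and an amendment removes that conflict.

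A second reply is that patients who do badly on CBZ are part of the reason for testing EA. The Introduction refers to patients who cannot tolerate high doses, and the Discussion to patients who stop because of poor tolerability. This stands against a broad exclusion. A reader might infer that anyone unable to tolerate 600 mg per day should be kept out. The documents do not support that: such a patient may still use 200 mg as rescue, and a broad exclusion could remove patients whom the trial is meant to inform.

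**Conclusion.** The point holds as a minor participant-safety gap. CBZ is the sole permitted rescue, other treatment outside the study sessions is barred, and the listed criteria do not screen for known hypersensitivity or contraindication to it. The conclusion assumes that the listed criteria and the rescue rule are complete as printed.

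Its size is unknown, and the group is narrow. Two stronger readings are tempting but unsupported:

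- **That a large share of participants would lack rescue**, taken from the 40% to 60% or 43.6% figures. Those count any adverse effect, which is not the same as being unable to take the drug.
- **That the VAS or BAI comparison is biased.** Nothing in the article shows how many such patients would enrol or how they would divide between arms, so no effect on the outcomes is claimed.

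**What to change.** Add exclusion (7) to the Exclusion criteria and to Table 2: *known hypersensitivity or contraindication to carbamazepine, or previous inability to take it even at the 200 mg rescue dose*. Check it against the treatment history already taken at screening. Patients intolerant only of higher doses stay eligible and use rescue at the dose they tolerate.

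Cost: one line in an amendment and a few more screen failures, number unknown.

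If the sponsor prefers to keep these patients, name one alternative rescue drug under Rescue medications, with drug and dose chosen by the sponsor's clinicians. Record it in the same way as CBZ, and count it in the rescue covariate and in the user and non-user strata under Statistical methods. Cost: a second drug to document, and a rescue variable that no longer means CBZ alone.

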### Outcome assessment

#### Primary outcomes

This study adopted dual primary endpoints: changes in BAI score and VAS score from baseline to week 4 post-treatment and week 16 follow-up phase, to fully assess the proposed “dual regulatory effect” of EA in TN patients with anxiety.

The BAI is a widely used anxiety scale for psychological assessment of patients and self-assessment in the general population. It was created by the team of American scholar Aaron T. Beck in 1988, with a total of 21 self-report questions (34). Notably, the scale is primarily designed to measure the degree of anxiety and to evaluate the therapeutic effects of anxiety treatment. The BAI adopted the 4-point Likert scale, ranging from 0 to 3 points for each question, based on the following criteria: ‘0′ means not at all; ‘1′ means mildly, with little annoyance; ‘2′ means moderately, feeling uncomfortable but tolerable; ‘3′ means severely, unbearable. The total score is the sum of all questions, ranging from 0 to 63 points, with a higher total score indicating a greater degree of anxiety. Generally, a participant with a total score between 0 to 7 points is considered to have basically no anxiety symptoms, while 8 to 15 points means mild anxiety, 16 to 25 points is moderate anxiety, and above 26 by severe anxiety.

Pain intensity will be evaluated using a 10-cm VAS anchored by ‘0′ (no pain) on the left and ‘10′ (worst pain imaginable) on the right. Participants will be asked to mark the point on the line that best represents their current pain intensity. The distance in centimeters from the ‘0′ end to the mark will be measured and recorded as the pain score. The *International Association for the Study of Pain (IASP)* recommends using the VAS score to assess pain intensity in patients with neuropathic pain, and to validate pain intensity relief with a particular therapy in a clinical trial (Grade A) (35).

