**Methods:**

This single-center, prospective, randomized controlled trial will recruit 60 TN patients with anxiety. All patients will be randomly assigned to the EA or sham EA group in a 1:1 ratio via a computerized central randomization system. The total trial duration is 18 weeks, including a 2-week baseline phase, a 4-week treatment phase, and a 12-week follow-up phase. Participants who meet the inclusion criteria will receive active EA or sham EA treatment for 60 min, three times a week, for 4 weeks.

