**Planned Outcomes:**

The primary outcome is the change of Beck Anxiety Inventory score and Visual Analog Scale score from baseline, while the BPI-Facial scores will be regarded as the secondary outcomes. All adverse effects will also be assessed during the study period. Outcome measures will be assessed at pre-intervention, post-intervention (week 4), and at the end of follow-up (week 16).

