### Sample size

Sample size estimation was performed by the “*Powerandsamplesize.com*” online website (31). This study is the first to explore the therapeutic effect of EA for TN with anxiety. Based on our pilot data with emotion scores between groups [EA group: 3.9 (1.2); control group: 1.2 (0.8)] by using an independent two-sample *t-*test design, a minimum of 25 participants per group will be required (two-sided α = 0.05, power = 0.8). To account for a 20% dropout rate, the final sample size will be set to 30 per group (total *N* = 60). This ensures adequate power even with potential attrition.

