## Conclusions

This protocol describes a rigorously designed, randomized, controlled, assessor-blinded trial designed to investigate the efficacy and safety of EA for TN with anxiety disorders. The results of this study will determine whether EA can alleviate the pain intensity while reducing anxiety symptoms for TN. These findings will be pertinent in determining complementary treatment options for TN with anxiety disorders in clinical practice.

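### Four primary comparisons (two scales at two visits) have no success rule, lead visit or alpha allocation, and the sample size covers one test of one unnamed score

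*Protocol article*

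**What the plan says.** The Primary outcomes section defines the primary set: "This study adopted dual primary endpoints: changes in BAI score and VAS score from baseline to week 4 post-treatment and week 16 follow-up phase". The abstract, under Planned Outcomes, names the same two scales ("The primary outcome is the change of Beck Anxiety Inventory score and Visual Analog Scale score from baseline"), lists weeks 4 and 16 as the post-baseline assessments, and ranks neither first.

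The Sample size section rests on one independent two-sample t-test. Its input is a pilot emotion score of 3.9 (1.2) in the EA group against 1.2 (0.8) in the control group. The scale and the visit are not named. The error rates are "two-sided α = 0.05, power = 0.8", and the result is that "a minimum of 25 participants per group will be required". There is no VAS input, no division of alpha and no statement about joint power.

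The Statistical methods section gives mixed models or ANCOVA as examples for the primary analyses. It names no success rule, lead visit, testing order or multiplicity method. The Conclusions section promises: "The results of this study will determine whether EA can alleviate the pain intensity while reducing anxiety symptoms for TN".

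**The concern.** The primary definition and the sample size describe different trials. One has four primary comparisons; the other has a single test at full alpha. Followed literally, the plan gives four tests at 0.05 and leaves open which pattern of results counts.

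Two things are at stake. If any one significant result can carry the claim, the nominal 5% does not hold. And with a mixed result, such as BAI at week 4 only or VAS at week 16 only, the same data could be reported as success or as failure once they are known. The sample size section does not help, because it does not address the primary set at all.

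**Working it through.** **Inputs from the protocol article.** Two endpoints and two visits (Primary outcomes). Two-sided alpha 0.05, power 0.80, pilot figures 3.9 (1.2) and 1.2 (0.8), 25 per group (Sample size). Allocation 1:1 (abstract, Methods). The bracketed pilot figures are read as SDs.

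**Assumed, because not given.** The correlations between the test statistics, taken from 0 to 0.9.

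**Step 1: the plan's own figure.**
- Common SD = √[(1.2² + 0.8²)/2] = √1.04 = 1.02.
- Standardised difference = (3.9 − 1.2)/1.02 = 2.65.
- n per group = 2(1.960 + 0.842)²/2.65² = 2.24, rounded up to 3.
- Exact noncentral t: 3 per group gives 68% power and 4 gives 87%.

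The stated 25 is not reproduced. Other readings (SD of 0.8, 1.2 or 2.0; one- or two-sided; power up to 95%; alpha 0.0125) give 2 to 19 per group. Working backwards, 25 per group gives 80% power for a standardised difference of about 0.81.

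**Step 2: number of comparisons.** 2 endpoints × 2 visits = 4.

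**Step 3: false-positive rate if any win counts, each test at 0.05.**
- Four independent tests: 1 − 0.95⁴ = 18.5%.
- Correlated tests were simulated as multivariate normal with 1,000,000 draws. The cross-correlation (different endpoint, different visit) is the product of the endpoint and visit correlations.

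| Endpoint correlation | Visit correlation | Any of four |
|---|---|---|
| 0 | 0 | 18.6% (exact 18.5%) |
| 0.5 | 0.5 | 16.2% |
| 0.7 | 0.7 | 13.7% |
| 0.9 | 0.9 | 9.8% |

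- With the same correlation between all four tests: 13.0% at 0.7 and 9.4% at 0.9.
- Two endpoints at one visit only: 1 − 0.95² = 9.75% if independent, 8.4% at correlation 0.7.
- These rates count significance in either direction. Counting only false wins for EA, four independent tests give 1 − 0.975⁴ = 9.6% against a nominal 2.5%.

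**Step 4: power, on two bases that disagree.**
- *Printed pilot figures (difference 2.65).* Power exceeds 99.9% at 24 to 30 per group, even at alpha 0.0125, and even for all four tests jointly if each had that effect.
- *Assumption that each test has exactly 80% power.* Both endpoints at one visit: 0.8² = 64% if independent, 71% at correlation 0.7. All four: 0.8⁴ = 41% if independent, 60% with both correlations at 0.7.

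The document cannot decide between these. The first basis concerns one unnamed score at an unnamed visit, and the second has no source for VAS.

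**The case against.** A reader might infer that the trial must have either an inflated error rate or less than 80% power. The documents do not support that, for two reasons.

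- **The choice is not exhaustive.** Suppose each test has 80% power at 0.05. Bonferroni over the four tests, with any win counting, holds the error rate at or below 5% and keeps 84% to 98% power for at least one win (correlations 0 to 0.7). A fixed testing order also holds 5% and leaves the first test at 80%.
- **The power loss cannot be derived.** The 64% to 71% takes 80% per test as given, while the printed pilot figures imply far more. On those figures, multiplicity costs practically no power.

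Two further points deserve weight. The wording on a dual regulatory effect, and on relieving pain while reducing anxiety, leans towards requiring both endpoints. If both were required at a single visit, the error rate would not be inflated. But that wording states an aim, not a decision rule, and it does not settle the visits.

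Also, this is a journal article, and a statistical analysis plan that is not shown may give a multiplicity method. The absence of such a method alone would be no finding. What stands is what the article itself fixes: a four-part primary definition beside a single-test sample size. A later adjustment would not make that calculation cover the primary set.

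**Conclusion.** The point holds on the primary definition and the error rate. Four comparisons are primary, and the article fixes no success rule, lead visit or alpha allocation. Under an any-win reading at unadjusted 0.05, the false-positive rate is about 14% to 18.5% for correlations of 0 to 0.7, and about 9% at 0.9. These figures depend on the any-win reading, which the article neither adopts nor rules out, and on the assumed correlations.

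On power, the supportable conclusion is that it is not established for the dual objective. No VAS effect or SD is stated, and 25 per group does not follow from the printed inputs. The 64% to 71% for both endpoints at one visit is conditional on 80% per test and should not be reported as this trial's power.

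**What to change.** Before unblinding:

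1. Name one primary visit, for example week 4, the end of treatment. The article does not rank the visits, so the sponsor must choose.
2. Require both BAI and VAS to reach two-sided p<0.05 at that visit. This matches the dual aim and needs no alpha split.
3. Make the other visit key secondary, tested only if step 2 succeeds. Another prespecified alpha-controlling scheme, such as a fixed order or Holm, would also do.
4. Rewrite the Sample size section so that power refers to the chosen rule. Name the scale and visit behind the pilot figures, give effect and SD assumptions for both BAI and VAS, and state the assumed correlation.

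The cost is wording in the outcome and sample size sections and a registry update. The downside is that the restated power may be less favourable. As an illustration, take a standardised difference of 0.81 on both endpoints and no correlation between them. Joint power of 80% needs √0.8 = 89.4% per test: 2(1.960 + 1.250)²/0.81² = 31.4, so 32 evaluable per group against the stated 25.
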